#### Blood flow restriction cycling group

The BFR-C group will complete an intermittent protocol of 10 min cycling, 20 min rest, 10 min cycling. During these sessions, participants in the BFR-C group will have a blood flow restriction cuff fitted to the proximal end of each thigh, which will be inflated continuously at 50% of a pre-determined limb occlusion pressure (LOP) throughout the full duration of cycling. Participants will be required to cycle at an RPE of 15 (‘Hard’ on the Borg 6 to 20 scale [51]), expected to be equivalent to at least 60% of APHR_max_ for each 10 min cycling period. The prescribed volume and intensity represents a balance between prior blood flow restriction protocols and those utilised in the aerobic training components of HD studies, while accounting for potentially very low levels of physical function among the participants [6, 8, 52].

#### Blood flow restriction procedure

Blood flow restriction will be applied using an automatic tourniquet system (A.T.S 3000, Zimmer Inc., OH, USA). The ATS produces a defined, controlled pressure via adjustable pneumatic cuffs (52 cm long, 10.5 cm wide; bladder length 45 cm, bladder width 8 cm). The pressure is regulated to control for changes in muscle contractile pressures under the cuff in such a way that the occlusive pressure applied to the limb is constant.

The cuffs will be applied to the proximal aspect of the thigh prior to commencing exercise, and gradually inflated, as detailed by Abe et al. (2006) [25]. Blood flow restriction pressure will be set at 50% of pre-exercise resting LOP. LOP will be calculated during a familiarisation session for participants allocated to the BFR-C group using a digital plethysmograph (Pulse Sensor, Zimmer ATS 3000) applied to the second toe [40, 53]. A seated or recumbent posture will be used for LOP as it most closely matches the posture that will be used during the exercise training sessions. To determine LOP, the pneumatic cuffs are inflated to the point at which the plethysmograph can no longer detect blood flow to the toe (blood flow completely occluded). This will be done for each leg and repeated to ensure accuracy (<20 mmHg), and an average of these measures will be taken. The 50% LOP that is to be applied during exercise training sessions does not fully occlude the limb in this manner, and allows for continuous blood flow during exercise.

#### Cycling group

The CYC group exercise training sessions will require 20 min continuous cycling at an equivalent intensity to the BFR-C group. However due to the absence of blood flow restriction, the equivalent intensity is often reported to have a lower RPE and mildly reduced heart rate response, regardless of exercise modality [38, 54, 55]. As such, the target RPE will be 12 (‘light to somewhat hard’ on the Borg 6 to 20 scale [51]) for the CYC group, which is expected to equate to at least 50% APHR_max_. This intensity is recommended for intradialytic aerobic exercise in the Exercise and Sport Science Australia (ESSA) position statement on exercise for chronic kidney disease [20]. This volume is reflective of protocols used by other studies examining exercise training among patients with ESKD, and represents a “normal” exercise training prescription for patients with ESKD [22, 56].

#### Progression

In order to ensure that training sessions maintain a sufficient intensity for all exercising participants, resistance applied to the pedals, cadence, or a combination of both variables will be adjusted on a session-by-session basis by a trained exercise physiologist such that the required RPE target (indicative of sufficient subjective intensity) is achieved. This accounts for any illness or excessive fatigue that may affect exertion during any given session. A rolling two-week average of RPE will be monitored (on the 6–20 Borg’s RPE scale [51]) to ensure progressive overload is being achieved over the course of the 3-month intervention.

#### Usual care control group

Participants allocated to the usual care control group will receive no additional access to exercise training and will receive minimal advice regarding exercise training throughout the study. Participants randomised to the usual care control group will be given access to an accredited exercise physiologist member of the research team, free of charge if they would like to discuss the benefits of commencing exercise training upon completion of the study.

### Data collection

Data collection will occur at baseline (T_1_) and 12 weeks (T_2_), with testing to be completed at the treating HD unit prior to the commencement of the participants’ HD session. Personal information, including relevant medical history will be collected prior to the initiation of testing or intervention upon receiving participant consent. This will include patient characteristics of age, gender, time in months that the participant has been receiving HD (dialysis vintage), basic anthropometric measures (height, weight, and BMI), relevant comorbidities and medications, transplant status, and type of dialysis access. Some or all of which may be taken, with approval, from the case file at the HD unit. The remaining data collected will include all measures of muscle function and physical function. Body composition scans will be performed on a non-dialysis day, separate from other testing procedures for participants who opt-in to this aspect of testing. Additional pathology measurements will include haemoglobin, albumin, potassium, parathyroid hormone, phosphate, urea reduction ratio (URR), creatine kinase and lactate. These measures will occur as part of routine pathology tests where possible, or will be requested out-of-cycle to coincide with the necessary period of the training intervention. Data will be coded and stored securely at Deakin University. Data collected from those who withdraw from the study will not be used for statistical analyses. This has been accounted for when completing the power analysis, with an additional 20% added to the target sample size. Attrition may be for a number of reasons, which will be ascertained upon withdrawal where possible.

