Heterogenous methodology, prescription and reporting among ESKD exercise studies make it difficult to draft guidelines on the dosage and mode of exercise training to derive the best outcomes for ESKD patients [8, 19]. The current guidelines for exercise training with ESKD recommend it encompasses aerobic (4 sessions; 45 mins), resistance (2 sessions; 20 mins), and flexibility (7 sessions; 10 mins) exercise [20]. The cumulative time commitment for these recommendations is substantial, and would require training on both dialysis (during first 2 h of dialysis) and non-dialysis days [20]. However, most randomised controlled trials examining exercise regimens in ESKD have only utilised aerobic training, most commonly stationary cycling [20]. Aerobic exercise training alone does not traditionally increase strength and hypertrophy, nor produce significant improvements in physical function, all of which are needed among this population [21].

Adherence to exercise training programs, regardless of aerobic, resistance or combined modalities, is also poor among ESKD patients, with more than 20% choosing not to participate, citing issues such as lack of time, lack of energy, too much trouble, and resistance training being too difficult [22]. Of those that chose to participate in exercise training, the dropout rate was more than 25% for programs utilising exercise training on non-dialysis days [22]. While there is still an increased dropout rate among patients with ESKD when exercise is completed intradialytically (approximately 17%) [22], it is lower than that seen on non-dialysis days. This suggests that intradialytic exercise is still preferable with regards to participant retention than exercise on non-dialysis days.

Resistance training poses further complications in the setting of a dialysis unit as the required equipment is cumbersome, and poses a high risk for cross-infection. Less cumbersome washable elastic resistance bands may be one option [23]. Exercise training during dialysis also needs to be completed in the first 2 h of dialysis sessions [24]. Therefore, finding a solution that may provide improvements in all key outcomes as efficiently as possible, allowing for completion during dialysis would be preferable.

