### Sample size calculation

The most relevant outcome for blood flow restriction training studies is knee extensor muscle strength, and this was used as the main primary outcome measure for calculating required sample size. Based on data from previous blood flow restriction research [25, 29, 32, 33], and previous exercise for ESKD research [18, 42, 43], the projected percentage changes in knee extensor muscle strength for each of the three groups are CON = −3%, CYC = 2%, BFR-C = 12%. The common standard deviation within group, based on the prior research was determined to be 15. Thus, to achieve a power of 80% at an α level of 0.05, 20 participants per group will be required to detect a difference between the expected means for percentage strength improvement. However, based on previous work conducted by this research group a conservative attrition rate of 20% is expected over 3 months due to voluntary patient withdrawal, death, additional hospitalisation, transfer to another facility, or patients receiving transplants [23]. Thus, a total of 75 participants will be recruited and randomly allocated to one of the three groups.

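### Discarding all data from participants who withdraw makes every analysis a completers-only comparison, and inflating the sample size does not cure the resulting risk of bias

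*Protocol article*

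**What the plan says.** The rule is in the Data collection section of the protocol article: "Data collected from those who withdraw from the study will not be used for statistical analyses". It makes no exception for data already collected. The reason given is: "This has been accounted for when completing the power analysis, with an additional 20% added to the target sample size".

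The Sample size calculation section gives the scale, "a conservative attrition rate of 20% is expected over 3 months", and the causes, "due to voluntary patient withdrawal, death, additional hospitalisation, transfer to another facility, or patients receiving transplants". It plans 20 analysed participants per group and recruits 75 in total.

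Other sections bear on the point:
- Randomisation takes place before familiarisation and baseline testing. Participants and clinical staff cannot be blinded once the intervention starts (Randomisation).
- Outcomes are measured at baseline and 12 weeks only (Data collection).
- The arms ask different things of patients: cycling at RPE 15 with inflated thigh cuffs, cycling at RPE 12, or no exercise (Exercise intervention and its subsections).
- The analysis is a one-way ANOVA with Tukey comparisons (Statistical analysis). No section offsets the exclusion.

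**The concern.** Randomisation makes the three groups comparable as allocated. Removing people for something that happens after allocation can undo this, and recruiting more people does not repair it. A larger sample of completers is still a sample of completers. Offering the inflated sample size as the answer treats a question of bias as one of precision.

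Some listed causes of attrition, notably death, hospitalisation and voluntary withdrawal, plausibly go with poor strength and walking ability. Reasons for leaving that come from the training itself can arise only in the exercise arms, and may differ between the two regimens. The groups left at 12 weeks may therefore differ for reasons other than treatment effect. The rule covers all analyses, so every primary and secondary outcome is exposed.

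This is a stated decision about the analysis, not a detail left to a fuller document.

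**Working it through.** **Reproducing the plan's figure.** Inputs from Sample size calculation: expected percentage changes in strength "CON = −3%, CYC = 2%, BFR-C = 12" (per cent), common SD 15, alpha 0.05, 20 per group, 20% attrition.

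- Grand mean = (−3 + 2 + 12)/3 = 3.67. Sum of squared deviations = 44.4 + 2.8 + 69.4 = 116.7. Cohen's f = √(116.7/3)/15 = 0.416.
- The noncentrality of the omnibus F test with 20 per group is 20 × 116.7/225 = 10.4, which gives power of 80.9% (78.6% with 19 per group). The stated 20 is reproduced.
- 20/(1 − 0.20) = 25 per group, or 75 in total. The stated 75 is reproduced. (Adding 20% literally would give 72, so the wording is loose but the figure is right.)
- Expected losses: 0.20 × 75 = 15, leaving 60 analysed.

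**Bias of a completers-only contrast.** Let d be the proportion lost in an arm and g the completers' mean change minus that of the dropouts. The completers' mean then exceeds the all-randomised mean by d × g. For arm A versus arm B, the bias is d_A·g_A − d_B·g_B. The documents give no dropout rate by arm and no outcomes for dropouts, so every g below is an assumption.

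*Illustration.* Exercise-arm dropouts change like CON (−3%), CON dropout is unrelated to outcome, and d is the same in all arms. Then g = 12 − (−3) = 15 in BFR-C, 2 − (−3) = 5 in CYC, and 0 in CON.

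| d | BFR-C vs CON: 15d (planned 15) | BFR-C vs CYC: 15d − 5d = 10d (planned 10) |
|---|---|---|
| 10% | 1.5 | 1.0 |
| 20% | 3.0 | 2.0 |
| 30% | 4.5 | 3.0 |

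If BFR-C dropouts instead changed like CYC (+2%), and dropout in the other two arms were unrelated to outcome, both contrasts would be overstated by 10d.

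*Other patterns, exercise arm versus CON:*
- 20% dropout and a 10-point gap in both arms: 0.20 × 10 − 0.20 × 10 = 0.
- 20% dropout, 10-point gap in CON only: −0.20 × 10 = −2.0, against exercise.
- 28% versus 12% dropout, 10-point gap in both: 2.8 − 1.2 = +1.6.

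**False positives.** Suppose there is no true difference among all randomised, 20% leave each arm, and only exercise-arm dropout is informative. In a simulation of a two-sample t test (20 completers per arm, SD 15, 20,000 runs), significant results favouring exercise rose from 2.5% to about 4.1%, 6.1% and 8.8% for gaps of 5, 10 and 15 points. This is simpler than the planned ANOVA with Tukey comparisons and shows scale only.

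**Power if all randomised are analysed.** Under the illustration at d = 20%, the means become CON −3, CYC 0.8 × 2 + 0.2 × (−3) = 1, and BFR-C 0.8 × 12 + 0.2 × (−3) = 9. The sum of squared deviations is 28.4 + 1.8 + 44.4 = 74.7. With SD held at 15:
- 25 per arm: noncentrality 25 × 74.7/225 = 8.3, power 71.5%.
- 20 per arm with 12-week data: noncentrality 6.6, power 60.6%.
- 31 per arm (93 in total) would be needed for at least 80%.
- If the planned means held for everyone and all 25 per arm were tested, power would be 89.5%.

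**The case against.** The strongest objection is that the direction and size of bias are unknown. No section gives dropout by arm. Equal dropout with equal gaps gives no bias, and informative dropout in CON alone reverses it. This stands, and it limits the point to exposure to bias.

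Second, the rule applies to those who withdraw from the study. It does not name people who miss sessions or stop cycling, and Exercise intervention lets those who cannot finish a bout do as much as they can. This also stands. The text does not say whether someone who stops exercising but attends at 12 weeks counts as withdrawn, and that needs settling.

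Third, death, transplant or transfer may leave no 12-week value under any rule, and many who withdraw will have at most baseline data. Less outcome data may therefore be discarded than 15 of 75 suggests. This is fair, but it argues for a plan for missing values, not for exclusion.

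Two stronger readings are tempting but unsupported:
- A reader might infer that the protocol itself says patients leave exercise programmes over time, energy or difficulty. The Background attaches these reasons ("citing issues such as lack of time, lack of energy, too much trouble, and resistance training being too difficult") to people who chose not to take part. It gives the dropout rates separately, without reasons.
- A reader might infer that the rule hides how well restricted cycling is tolerated. Reasons for attrition are to be sought at withdrawal where possible (Data collection), and symptoms and adverse events are monitored (Inclusion and exclusion criteria). Nothing stops withdrawals being counted by arm.

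**Conclusion.** The point holds as exposure to bias. The protocol fixes a completers-only analysis and defends it with an argument about numbers. The sample-size arithmetic is sound, but it does not answer the problem.

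If exercise-arm dropouts change like controls, CON dropout is uninformative and 20% leave each arm, the overstatement is 3.0 of 15 points for BFR-C versus CON and 2.0 of 10 for BFR-C versus CYC, a fifth of each planned difference. It would be wrong to set the 15d figure against the BFR-C versus CYC difference, because CYC loses participants too and the net figure is 10d. A reader might also conclude that the rule must favour exercise. That is plausible, given the unequal burden and the lack of blinding, but not established.

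Confidence is high that the rule is stated and that the inflation does not justify it. The size and direction of bias rest on the assumptions given.

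**What to change.** Replace the sentence in Data collection with a rule on these lines:
- Analyse all randomised participants in their allocated group.
- Use all data already collected, unless the participant withdraws consent to its use.
- Define withdrawal from the study separately from stopping exercise. Invite those who stop exercising and can still be tested to the scheduled 12-week assessment.
- Handle missing 12-week values with a likelihood-based model or multiple imputation, with a sensitivity analysis that imputes exercise-arm dropouts from CON.
- Keep the completers analysis as supplementary.

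Keep the 20% inflation, described as an allowance for missing 12-week data, and say that the stated 80% power applies to the completers' assumptions.

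The cost is some rewording, a little more analysis, and the effort of testing people who have stopped exercising, which will not be possible for all of them. The estimated effect may be smaller. Under the illustration at 20% dropout, power falls to about 72% with 25 per arm or about 61% with 20. The sponsor should weigh this openly, because keeping 80% under that assumption would take 93 participants instead of 75.

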### Primary outcome measures

#### Lower-limb muscle strength

Maximal lower limb muscle strength will be determined using three-repetition maximum (3RM) knee extension (HS-LE, Life Fitness, Victoria, Australia) [57]. A 3RM knee extension test measures the maximum weight that can be lifted for three consecutive repetitions of a knee extension exercise with good technique and full range of motion. The 3RM result will be input into a formula to derive equivalent one-repetition maximum for each participant [58].

#### Physical function

Objective physical function will be measured using the 30-s sit to stand test (STS30), the timed up and go test (TUG), and the six-minute walk test (6MWT).

The STS30 measures lower limb muscle strength and function and requires participants to stand from a chair and then return to the seated position as many times as possible in 30 s [59]. The test has also displayed strong comparative validity to lower extremity 1RM strength testing, particularly among community-dwelling older adults [59]. It has also demonstrated a high level of reliability among ESKD patients undergoing HD (ICC = 0.93) [60].

The TUG is a measure of dynamic balance and mobility requiring participants to stand from a chair, walk to and then around a cone placed 3 m away, walk back to the chair, and sit back down as quickly as possible. This test will be repeated three times, and an average time taken for accuracy purposes [61]. The TUG strongly reflects gait speed among older adults, and has shown strong test re-test reliability not only among older adults, but in ESKD patients undergoing HD (ICC = 0.91–0.96) [62–64].

The 6MWT is a self-paced assessment of aerobic capacity, and a strong index of all cause morbidity in older adults [65]. It requires participants to walk laps of a straight 30 m course with the objective to cover as much distance as possible in the six-minute duration [65]. The 6MWT is a reliable measure for patients with ESKD (ICC = 0.93–0.96) [60, 66]. It has also been validated against ⩒O_2_max for patients with ESKD, with moderate strength coefficients of correlation (*r* = 0.56–0.73) [11, 67].

### Secondary outcome measures

#### Muscle cross-sectional area and body composition

Total and regional body composition (lean mass, fat mass and percentage fat mass) will be assessed using iDXA (Lunar iDXA, GE Healthcare, Madison, WI). Muscle cross-sectional area around the femur diaphysis at 25% and 50% of femur length will be assessed using pQCT (XCT 3000, Stratec Medizintechnik, Baden-Württemberg, Germany), allowing for knee flexor and extensor musculature to be measured. Height and body mass will be assessed using a portable stadiometer and scales respectively.

#### Pathology measures

Pathology measurements will be taken during routine collections completed by the treating hospital. The exercise intervention will be timed such that these routine pathology measures occur within the 4 weeks prior to the commencement of the first training session (or prior to the 3 month usual care monitoring period for the CON). These additional measures will include haemoglobin, albumin, potassium, parathyroid hormone, and phosphate. URR will also be measured by the treating hospital as a part of patients’ quarterly pathology tests, providing it is within the 4 weeks prior to patients commencing their exercise intervention. If this cannot be achieved in a timely manner, an additional measure of URR will be requested for a single dialysis session prior to the commencement of the exercise intervention.

Two additional measures of URR, creatine kinase and lactate will also be required outside of the normal regimen for patients in either of the exercise training intervention groups, once during the first week of the exercise training intervention, and again during the final week of the exercise training intervention. An additional out-of-cycle measure of URR will also be required by participants in the usual care control group, unless this is scheduled to be completed within 2 weeks following their 3-month monitoring period for this study as a part of their quarterly routine pathology test. All measures are conducted at the beginning and upon completion of a single dialysis session to establish the difference in each marker over the course of that session. This will allow analysis of the impact of exercise and specific exercise intervention types (BFR-C and CYC) on dialysis adequacy, as well as providing objective proof that there is no major tissue damage as a result of the intervention.

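### Creatine kinase and lactate, sampled only in the two exercise arms and without an assured pre-training value, cannot prove that the intervention causes no major tissue damage

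*Protocol article*

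**What the plan says.** The Pathology measures section (under Secondary outcome measures) sets out the sampling of creatine kinase and lactate and the conclusion to be drawn from it.

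- **Who.** They are extra tests, with URR, "outside of the normal regimen for patients in either of the exercise training intervention groups". For CON the section adds only URR: "An additional out-of-cycle measure of URR will also be required by participants in the usual care control group". This is waived if a routine quarterly test falls in a set window: "unless this is scheduled to be completed within 2 weeks following their 3-month monitoring period".
- **When.** "once during the first week of the exercise training intervention, and again during the final week of the exercise training intervention".
- **How.** "All measures are conducted at the beginning and upon completion of a single dialysis session to establish the difference in each marker".
- **Conclusion claimed.** The sampling is described "as well as providing objective proof that there is no major tissue damage as a result of the intervention".

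The routine markers that the same section places before training are haemoglobin, albumin, potassium, parathyroid hormone and phosphate, with URR handled separately. Creatine kinase and lactate are not among them.

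The Data collection section gives baseline and 12 weeks as the assessment times. Its list of pathology tests ends with "urea reduction ratio (URR), creatine kinase and lactate" and has no restriction by arm.

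**The concern.** The claim has two parts: that damage is absent, and that the intervention is what has been shown not to cause it. The second part needs a comparison with dialysis without exercise, or at least with a value from before training. The schedule provides no such CON sample and does not guarantee a pre-training one. The first part needs enough participants to exclude a rate of damage that would matter, and the trial was sized for knee extensor strength.

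The Background calls blood flow restriction exercise a novel addition for patients with end-stage kidney disease, and the pilot data that it mentions are haemodynamic. These two markers are therefore the only laboratory evidence on tissue damage that the protocol names. If the stated conclusion is carried into the report, an unremarkable set of results would be presented as more than the design can show.

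**Working it through.** **1. The plan's own sample size.** The Sample size calculation gives mean changes of −3%, 2% and 12%, SD 15, α 0.05 and power 80%. The grand mean is 11/3 = 3.67 and the squared deviations sum to 44.44 + 2.78 + 69.44 = 116.67. Cohen's f = √(116.67/3)/15 = 0.416. A three-group one-way ANOVA (noncentral F) has power 78.6% with 19 per group and 80.9% with 20, so 20 is reproduced. With 20% attrition, 60/(1 − 0.20) = 75, or 25 per arm if allocation is equal. This calculation concerns strength. The protocol states no size, threshold or margin for creatine kinase or lactate.

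**2. What is sampled.**

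| Arm | Before training | First week | Final week or follow-up |
|---|---|---|---|
| BFR-C | not assured | start and end of one session | start and end of one session |
| CYC | not assured | start and end of one session | start and end of one session |
| CON | none | none | none (URR only) |

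Each exerciser therefore gives 2 sessions × 2 draws = 4 values per marker, and CON gives none. Training takes place three times per week, so the first-week draw could fall at the first, second or third session. Only at the first would its opening draw precede training.

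**3. What can be estimated.** Let d be the mean within-session change due to dialysis alone, e the part added by the CYC prescription, and r the further part added by BFR-C.

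- CYC estimates d + e.
- BFR-C estimates d + e + r.
- BFR-C − CYC estimates r. This is a randomised contrast of the whole BFR-C prescription (cuffs, higher target exertion, two bouts with a rest) with CYC.
- Neither e nor e + r can be estimated, because nothing estimates d. If d is negative, an observed change of zero in BFR-C is compatible with e + r = −d, which is a rise due to exercise.

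The first-week and final-week start-of-session values allow a crude comparison over the training period. Without CON, however, it mixes training with any drift over time, and the first-week value is a baseline only if it comes from the first session.

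**4. What a null result would exclude.** As an illustration, suppose that major damage is counted as a yes/no event. With zero events in n participants the one-sided 95% upper limit is 1 − 0.05^(1/n).

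| n | Who | Upper limit |
|---|---|---|
| 20 | BFR-C completers | 13.9% |
| 25 | BFR-C allocated | 11.3% |
| 40 | completers, both exercise arms | 7.2% |
| 50 | allocated, both exercise arms | 5.8% |

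At a true rate of 5%, the chance of seeing no event is 0.95^20 = 36% with 20 participants and 0.95^40 = 13% with 40. The completer rows fit the plan better, because the Data collection section leaves data from withdrawn participants out of the analysis.

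**The case against.** The best defence is that the comparison that matters most is present. Restriction is the new element, the hypothesis is benefit beyond traditional cycling, and CYC is a concurrent randomised arm on dialysis with the same 20 minutes of cycling. This stands. A reader might infer that the markers say nothing about the intervention, and the documents do not support that. BFR-C versus CYC is informative about the added effect of the restriction prescription, though not about exercise itself.

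Four further points limit the finding, and each stands:

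- A reader might infer that only one session is ever sampled. There are two sampled sessions, and their starting levels can be compared.
- A reader might infer that safety goes unmonitored. The Inclusion and exclusion criteria section provides for monitoring of symptoms and adverse events, with reporting to two ethics committees.
- A reader might infer a firm contradiction between the two sections on who is sampled. The Data collection list is general, and it adds that tests may be requested out of cycle to fit the training period. The sections are better called unaligned.
- The zero-event limits would apply to any group of that size, and the protocol defines no such event for these continuous markers. They show scale and do not measure a fault in the schedule.

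None of this supports the word proof.

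**Conclusion.** The concern holds for the biomarker inference only. As scheduled, creatine kinase and lactate can estimate the added effect of BFR-C over CYC on within-session change, and can describe a rough change in starting level over the programme. They cannot separate exercise from dialysis, and they cannot establish that damage is absent. Zero events would still be compatible with true rates up to 13.9% (20 participants) or 7.2% (40).

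The reading rests on the detailed schedule in the Pathology measures section taking precedence over the general list in Data collection. The limits rest on 20 completers per arm, equal allocation and a yes/no definition of damage that the protocol does not give. No primary outcome is affected. The correction still matters, because it changes what the trial may conclude about tissue damage.

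**What to change.** 1. In Pathology measures, remove the claim of proof. State instead that two quantities will be reported, each with a 95% confidence interval: the BFR-C minus CYC difference in within-session change, and the change in start-of-session level from the first to the final week. Make no claim of proven absence of damage.
2. Add creatine kinase and lactate to the start and end draws of the CON follow-up URR session that the section already foresees. Because the arms are randomised, a follow-up comparison with CON is valid without a CON baseline. In the notation above it supplies d, so that e and e + r can be estimated. A baseline addition in CON is not assumed to be equally easy, since the text ties the pre-training URR to starting exercise and does not explicitly give one to CON.
3. Fix the first-week sample in both exercise arms at the first training session, so that its opening draw precedes training.
4. Make the Data collection section name the same arms and times as Pathology measures.

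Items 1 and 4 cost only wording, and item 3 fixes the date of a sample already planned. Item 2 costs two assays on each of two draws per CON participant, at most 25 × 2 × 2 = 100 assay results. CON participants who would have relied on a routine quarterly URR may need the out-of-cycle sample instead.
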